# Abbreviations

| CDI | Child development index |
| --- | --- |
| CRF | Case report form (data collection document) |
| CRF | Case report form |
| GCP | Good Clinical Practice |
| HAZ | Height-for-age Z-score |
| HSP | Human Subject Protection |
| IRB | Institutional Review Board |
| ITC | Inpatient clinic – for the treatment of complicated SAM |
| LNS-LQ | Large-quantity lipid-based nutrient supplements |
| MAGNUS | Milk affecting growth, cognition and the gut in child stunting |
| MDAT | Malawi development assessment tool |
| MPI | Milk protein isolate |
| MUAC | Mid-upper-arm circumference |
| OTC | Outpatient clinic - for the treatment of uncomplicated SAM |
| SAE | Serious adverse event |
| SAM | Severe acute malnutrition |
| SOP | Standard operating procedures |
| SPI | Soy protein isolate |
| UNCST | The Ugandan National Council of Science and Technology |
| VHTs | Village health teams (refers to one or several people) |
| EED | Environmental enteric dysfunction |
| WAZ | Weight-for-age z-score |
| WHZ | Weight-for-height z-score |
| WP | Whey permeate |

# Definitions of terms

| Stunting | Also known as linear growth faltering or short-for-age. Defined as height-for-age Z-score < -2. |
| --- | --- |
| Milk protein isolate (MPI): | A milk ingredient obtained by isolating the protein components of milk (casein and whey proteins). Milk protein isolate contains a minimum of 90% milk proteins. |
| Lipid based nutrient supplements (LNS): | A generic term for fortified, lipid-based ready-to-use supplementary or therapeutic products which are modified in their energy density, protein, fat or micronutrient composition to help meet the nutritional requirements of specific populations. They are currently in use in the treatment or prevention of child malnutrition. |
| Whey permeate (WP): | A product of whey ultrafiltration. Proteins are removed, contains over 80/85% lactose and milk minerals. |
| Lactose | A disaccharide which is the main carbohydrate component of human breast milk (approx. 7%) and makes up approximately 4.8% of cow’s milk. |
| Milk minerals | Highly bioavailable minerals found in milk; potassium, phosphorus, magnesium, calcium, sodium and to a lesser extent zinc. |
| Environmental enteric dysfunction | A generalised inflammatory disorder of the small intestine that is thought to be widespread among children living in low-income country settings. |

# Summary of protocol

| **Title of Study:**  The role of milk protein and whey permeate in the growth and development of stunted children. | |
| --- | --- |
| **Acronym:**  MAGNUS – Milk affecting growth, cognition and the gut in child stunting | |
| **Study Code:**  D-222 | |
| **Funding:**  1) Arla Food for Health 2) Danish Dairy Research Foundation, 3) University of Copenhagen, Department of Nutrition, Exercise and Sports. | |
| **Sponsor:**  University of Copenhagen, Department of Nutrition, Exercise and Sports  **Sponsor representative:**  [name], Professor, MD, PhD, University of Copenhagen, Section for Paediatrics and International Nutrition, Denmark | |
| **Principal Investigators:**  1) [name], Pediatrician, Epidemiologist, Head of Department of Paediatrics and Child Health, Makerere University, Uganda 2) [name], Professor, MD, PhD, University of Copenhagen, Department of Nutrition, Exercise and Sports, Denmark | |
| **Study Operations:**  Study Site: Site operations facilitated from two health centres in Jinja. Agreements with local government offices in Jinja and Mayuge districts to expand if further sites are needed. Central office in Jinja town. | |
| **Planned Study Period:**  First patient in: January 2020, Last patient out: June 2021 | |
| **Objectives:**  The primary objective is to assess the effects of supplementation with milk protein isolate (MPI) and whey permeate (WP) on linear growth in stunted children.  Secondary objectives are to assess the effects of supplementation with MPI and WP on child development, on anthropometric measurements, on body composition and blood haemoglobin concentration in stunted children. | |
| **Measurable Outcomes:**  Primary outcome: Knee-heel length (mm) and total length (cm) over 12 weeks.  Secondary outcomes: HAZ, WAZ, WHZ, weight gain (g), body composition (bioimpedance and skin folds), head circumference, MUAC, haemoglobin (Hb) and child development, based on the Malawi Developmental Assessment Tool (MDAT) over 12 weeks.  Tertiary outcomes: Growth factors [Insulin-like growth factor-1 (IGF-1), insulin], markers of nutrient status [ferritin, soluble transferrin receptor (sTfR), vitamin B12, vitamin A and folate], markers of systemic inflammation, intestinal inflammation and intestinal function [C-reactive protein (CRP), alpha-1-acid glycoprotein (AGP), myeloperoxidase (MPO), neopterin (NEO), alpha-1-antitrypsin (AAT), citrulline], gut microbiota (diversity and composition), and morbidity over 12 weeks. | |
| **Study participants:**  750 children aged 12 -59 months with a HAZ <-2. | |
| **Study design:**  A randomised, double-blinded, community trial, testing four different large-quantity lipid-based nutrient supplements (LNS-LQ) in a two-by-two factorial design. A fifth un-supplemented group is included as a reference. Shown in figure 1. | |
| \|  \|  \| + Milk protein isolate (MPI) \|  \| + Soy protein Isolate (SPI) \| \| --- \| --- \| --- \| --- \| --- \| \| Whey permeate  (+ WP) \| A. \| LNS-LQ + MPI + WP  n=150 \| C. \| LNS-LQ + SPI + WP  n=150 \| \| No whey permeate  (-WP) \| B. \| LNS-LQ + MPI – WP  n=150 \| D. \| LNS-LQ + SPI - WP  n=150 \|  \|  \| Family diet \| \| --- \| --- \| \| E. \| Reference n=150 \|   **Figure 1:** Four large-quantity lipid-based nutrient supplements (LNS-LQ) in a two-by-two factorial design. Reference group continues with family diet. n= number of children allocated. MPI: Milk protein isolate, WP: whey permeate, SPI: soy protein isolate | |
| **Study site and recruitment:**  Study clinics are run from selected community health centres. Recruitment will take place in villages located nearby these selected community health centers | |
| **Participant inclusion:**  If both inclusion and exclusion criteria are fulfilled and informed consent is given, children are randomly allocated to one of four LNS-LQ or to an un-supplemented group. | |
| **Criteria for inclusion:**   - Age 12 - 59 months - HAZ < -2 according to WHO growth standards (2006) - Care-taker able and willing to return for follow-up visits and agrees to phone follow-up - Living within the catchment area - Written informed consent given by parent/caregiver   **Criteria for exclusion:**   - SAM, defined as MUAC <115 mm OR WHZ<-3 OR bipedal pitting oedema - Medical complications requiring hospitalization. - Obvious disability that impedes eating capacity - Disability that makes length/height assessment problematic - Participation in another study which impacts on this study or previous enrollment in this study. - Family plans to move away from the catchment area in the next 6 months. - History or known allergy to peanuts or milk | |
| **Intervention:**  A supplementary food intervention. Of the 750 children included in the study, 600 are randomly allocated to one of four LNS-LQ upon inclusion and 150 are randomly allocated to no supplementation. All children receive nutrition counselling at inclusion. Those randomised to LNS are given one sachet of 100g per day in addition to the home based diet. Each 100g LNS-LQ sachet provides approximately 530kcal, provides up to half of the average daily energy requirements, and satisfies most of the estimated daily micronutrient requirements (age dependent). | |
| **Duration of intervention:**  12 week intervention. | |
| **Data collection and follow-up**  **[figure not shown]** | |
| **Figure 2:** Study design framework and time-points for data collection.  The 750 children with a HAZ <-2 are included and randomly allocated to one of four LNS-LQ or to a reference group. Supplemented children are provided one LNS-LQ sachet per day (in two-week allocations) over a period of 12 weeks. After inclusion, all children, irrespective of allocation are followed-up every 2-4 weeks until 12 weeks. | **[figure not shown]** |
| **Statistical Methods:**  Primary, secondary, and tertiary endpoints are analysed by means of longitudinal data analysis since repeated measurements are recorded per patient. | |

# Introduction

## Background

Stunting is the most prevalent form of malnutrition: it is estimated to affect one in every fourth child, or 149 million children globally [1]. While acute malnutrition has been steadily in decline over the last decade, stunting is a particular challenge in East Africa, where according to the WHO, absolute numbers are on the rise due to population growth [1]. Stunting is defined as having a height-for-age Z score (HAZ) that is less than -2, according to the WHO growth standards [2]. Stunting has been associated with increased risk of mortality, impaired immune function, and delayed physical and cognitive development [3]. The knock on effects from stunting have the potential to reduce physical capacity and economic productivity later in life [4], and in this way, widespread stunting also has the potential to impact on societal economic development. In Uganda, nearly one in three children under five are stunted, which is similar to proportions reported in the Busoga sub-region in Eastern Central Uganda [5]. It is of fundamental importance to find the means to prevent stunting for future generations, but is arguably equally important to find solutions to improving outcomes for those children who are already stunted. While the pathogenesis of stunting remains unclear, several risk factors have been identified such as; foetal growth restriction, exposure to unsanitary environments and nutritionally inadequate diets throughout the early years of life [6]. Many of these factors have been the target of intervention in recent years.

It is well established that adequate nutrient intake in the early years plays a crucial role in growth and cognitive development. A nationwide analysis reported that most of the Busoga sub-region is entering either a stressed or a crisis phase of food insecurity [7], and this is likely to exacerbate nutrient deficiencies. Moderate to severe anaemia among children in the Busoga Sub-Region are reported to be over 40 percent, 10 percent above the national average [5]. Such nutrient deficiencies may be further exacerbated by the presence of a generalised inflammatory disorder of the small intestine which is thought to be widespread among children living in settings where they are frequently exposed to conditions of inadequate sanitation and hygiene [8]. This enteric state called environmental enteric dysfunction (EED), may impair the appropriate absorption and utilisation of nutrients. While this condition is considered reversible, it is thought to be an important contributor to the aetiology of stunting in early life. In settings where food insecurity is a concern and where nutrient deficiencies are widespread, specially formulated, lipid-based nutrient supplements (LNS) can be of great benefit in filling the nutrient gaps in the home diet [9].

Often LNS supplements contain milk products. One reason for this is that studies from both low and high income countries shown that milk may have a growth promoting effect [10] and has been associated with increases in lean mass deposition, and benefits to cognitive function, even beyond the early developmental years [11]. To better understand the possible beneficial effects of milk, consideration can be given to the different milk ingredients separately. The two major types of protein in milk are casein and whey. They are thought to promote growth by stimulating growth factors IGF-1 and insulin. Milk proteins have a rich amino acid (AA) profile, containing all essential AAs; both branched and sulphur containing, which are important for lean tissue deposition [12].

Whey permeate is the portion of milk that contains the lactose and naturally occurring minerals, each may contribute unique growth stimulating effects. Whey permeate is approximately 80-85 percent lactose and may also have a prebiotic effect, stimulating the growth of beneficial bacteria in the intestine [13]*.* The highly concentrated and bioavailable milk minerals (potassium, phosphorus, magnesium, calcium, sodium and to a lesser extent zinc), may also play a role in bone mineralisation and lean tissue deposition [14].

Non-milk sources of protein, such as soy have also been used in LNS to stimulate growth [15–17]. Soy is one of the most amino acid rich sources of plant protein available. Dehulled soy is the most common soy protein used in supplements. Due to minimal processing however, dehulled soy contains phytates which can reduce the bioavailability of essential micronutrients including calcium, zinc and iron, and may also hinder protein absorption [18]. On the other hand, soy protein isolate (SPI) is over 90 percent protein and has been processed to remove the phytate content so that SPI has a high Digestible Indispensable Amino Acid Score (DIAAS).

A number of studies aiming to prevent stunting have seen some positive effects on linear growth and haemoglobin levels after provision of small daily doses of LNS during the first 1000 days of life [19–22]. A recently published meta-analysis confirms that the use of LNS in combination with complementary feeding is a more effective means to improve such outcomes than no intervention [23]. Overall however, the benefit on linear growth from supplementation with small quantity LNS has been limited [24]. It may be that the amount of milk protein provided in a 20g sachet is not adequate to replenish nutrient deficiencies and stimulate growth. In order to provide the equivalent of one glass of milk per day in children older than one year, a larger quantity of LNS is necessary [25] .

Lipid based nutrient supplements (LNS) have been developed in an effort to bridge the nutrient gaps and to encourage growth and repair in young children. While the first 1000 days are extremely important, there is also reason to believe that interventions after this stage can have a measurable impact on growth and cognitive development [9].This study will provide new and unique perspectives on child stunting in several ways. First this study explores the effects of milk ingredients (milk proteins and whey permeate) on growth, child development, body composition, haemoglobin and a number of functional outcomes. Furthermore, we explore the use of large quantity LNS (LNS-LQ) to improve outcomes of stunted children aged 12-59 months. The findings from this study will improve our knowledge on the value of milk ingredients in the treatment of child stunting before and beyond the first 1000 days as well as contributing to the base of knowledge in order to better prevent stunting.

## Study location and capacity building

The study is located in the Busoga subregion of Eastern Uganda and will be implemented at community health clinics in collaboration with the Department of Paediatrics and Child Health, Makerere University, Kampala, Uganda. Decisions concerning where study sites should be located have been made in collaboration with the District Health Officer (DHO) and the acting responsible of relevant community health clinics. Two Ugandan PhD students are included as co-researchers on the team. The study also involves qualified local nurses, nutritionists, child development officers, lab technicians, village health workers (VHTs), and where possible, masters students.

# Objectives

## Overall study objective

To assess the effectiveness of milk protein isolate and whey permeate in improving growth and development in stunted Ugandan children aged 12-59 months.

## Primary objective

To assess the effects of supplementation with milk protein isolate and whey permeate on; linear growth based on knee-heel length and total length.

## Secondary objectives

To assess the effects of supplementation with milk protein isolate and whey permeate on child development, blood haemoglobin concentration, and on anthropometric measurements including; height-for-age Z-score, weight-for-height Z-score, weight-for-age Z-score, mid-upper arm circumference, skin folds and body composition.

# Trial design

## Overall study design and duration

This is a randomised, double-blinded, community-based controlled trial, which tests the effects of whey permeate and milk protein isolate on growth in stunted children aged 12-59 months in a two-by-two factorial design (Figure 1). All of the 750 children included in the study receive nutrition counselling at baseline, of these, 600 will be randomised to one of four supplements for a 12 week duration. As a reference, a further 150 children will be randomised to continue with the family diet for 12 weeks. All children are followed-up at regular intervals during these 12 weeks. (Figure 2).

|  |  | + Milk protein isolate (MPI) |  | + Soy protein Isolate (SPI) |
| --- | --- | --- | --- | --- |
| Whey permeate  (+ WP) | A. | LNS-LQ + MPI + WP  n=150 | C. | LNS-LQ + SPI + WP  n=150 |
| No whey permeate  (-WP) | B. | LNS-LQ + MPI – WP  n=150 | D. | LNS-LQ + SPI – WP  n=150 |
|  |  |  |  |  |
|  |  |  |  | Family diet |
|  |  |  | E. | Reference group n=150 |

**Figure 1: Four large-quantity lipid-based nutrient supplements (LNS-LQ) in a two-by-two factorial design** (A, B, C and D). Reference group (E) continues with family diet. n= number of children allocated, MPI: Milk protein isolate, WP: whey protein, SPI: soy protein isolate

No supplementation

Supplementation

**Inclusion**

**12 wks/ Discharge**

E. Reference n= 150

Children HAZ <-2

N = 750

A. LNS-LQ n= 150

B. LNS-LQ n= 150

C. LNS-LQ n= 150

D. LNS-LQ n= 150

**Figure 2: MAGNUS study design framework.** 750 children with HAZ <-2 are included and randomised to one of four supplements or to a reference group. LNS-LQ is allocated for a fixed duration of 12 weeks after inclusion.. The reference group is not supplemented. LNS-LQ: Large-quantity lipid-Based Nutrient Supplement. HAZ: Height-for-age Z score

## Description of study flow and processes

### Community mobilisation

Prior to recruitment within a particular community, community leaders will be informed about the study to strengthen community engagement in support of pre-screening for the study.

### Pre-screening and referral

Village health teams (VHTs) will mobilise communities and refer children to a local pre-screening site within the community. The pre-screening team will screen children for stunting and severe acute malnutrition (SAM). Those identified as stunted are referred according to the SOP. Children identified as having SAM are referred to outpatient care (OTC) or inpatient care (ITC) for relevant treatment. Pre-screening data will be recorded with a pre-screening ID. The VHTs will be remunerated for their work in the study.

### Screening

Screening is carried out at the study site. All children screened are allocated a screening ID number. Study staff who are trained in taking anthropometrics will measure the child’s MUAC, weight, height/length and check for oedema. If the child is classified as being stunted without SAM, qualified clinical study staff will assess the child according to the remaining inclusion and exclusion criteria. If all criteria are met, the caregiver is taken through the informed consent process. If informed consent is given, the child is included in the study.

### Inclusion

Upon inclusion, children are allocated a unique study ID number and are taken through a registration process according to the relevant SOP.

### Baseline measurements

Following inclusion, baseline measurements are taken according to the relevant SOPs. An example of the site flow at baseline is provided in figure 3. The following measurements are taken/assessed at baseline: questionnaires of medical history, demographics and dietary information, clinical assessment is conducted, blood and stool samples are collected, anthropometrics of the mother (if available) and child are measured, bioimpedance and child development assessed. A full description of the data collected at baseline is provided in section 22.

### Nutrition counselling and training

All caregivers receive locally adapted nutrition counselling. If stool sample collections are not possible at the baseline clinic visit, the caregiver is given instruction and a kit for stool collection at home. Refer to the SOP for further detail.

**
[figure not shown]
**

**Figure 3: Basic study site flow.** Includes flow at baseline and for follow-up clinic visits. This is only a visual representation and may be subject to change. The SOP gives further detail. Measurements include sample collection at baseline and week 12 visits. LNS-LQ: Large-quantity lipid-based nutrient supplements; WASH: water, sanitation and hygiene.

### Random allocation

Thereafter, caregivers are informed of allocation to supplementation or the reference group. Those not allocated to supplementation are given a token of appreciation (given at each follow-up clinic visit), valued at around 5000 UGX but not more than 10 000UGX, for example clothes soap. If allocated to LNS caregivers are given training concerning appropriate use of LNS before they are allocated a two week supply. Prior to departure all caregivers are given a follow-up plan. Refer to the SOP for further details.

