# Strategies to improve and monitor adherence

It is a challenge to ensure that the participating child is the one receiving the LNS, due to home based caregiver administration. As such, several actions are taken to improve compliance.

- Siblings: We aim to only include one child per household in the study. However, if there are other young children in the household (6 months to five years), instructions and sachets will be given so that the caregiver receives extra rationing. This strategy aims to minimize the likelihood of sharing.
- Identification: Several methods are used to ensure that the correct child is matched to the correct study records, namely wrist bands and photo id. The SOP describes the use of these processes in detail.
- Accountability: Any distribution of sachet stocks will be logged by study staff. Additionally, when collecting new sachets, the caregiver is requested to return the empty sachets from their previous two week supply. This is to improve accountability on the part off the caregivers, and encourage against sachet redistribution or selling.
- Monitoring adherence: Trained study staff will make regular phone follow-up calls to the participant/caretakers to remind them of their clinic visits and enquire about stool sample collection or LNS adherence where applicable. At clinic visits and when the caregiver is collecting sachet stocks study staff will also enquire about LNS adherence.
- Incentives: Throughout the study, the child’s health will be monitored regularly. A travel reimbursement of not more than 20,000UGX will be provided to cover the cost of return transport and includes some allowance for e.g. food purchase during the day while at the clinic visit. Any caregivers attending with unsupplemented children will also receive a small token which can be appreciated by the whole family, for example clothes soap. The value will not exceed 10,000UGX.

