# Sample size

The sample size calculation is generic, based on the ability to detect differences in terms of standard deviations. Conservatively, we want to be able to detect a 0.35 SD or greater difference between any two groups with 5% significance and 80% power. For this, we need 129 children in each group, but to allow for 10% loss to follow-up, we will include 150 children in each group. However, given the factorial design, if there are no interactions between the two experimental interventions, we will be able to compare two groups of 300 children each, which will enable us to detect a difference as small as 0.24 SD. In the Treatfood trial, the SD of knee‐heel length at baseline was 18.1 mm [17]. Hence, a 0.24 SD difference corresponds to 4.3 mm. In secondary analysis, we will compare the 600 supplemented children with 150 unsupplemented. These group sizes will allow us to detect a 0.27 SD difference, corresponding to 4.9 mm.

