## House mapping and WASH assessment

At the first participant home visit study staff record the GPS coordinates of the home site location, in case home follow-up is needed at a later stage. Study staff also make a short assessment of WASH characteristics including; water source, basic sanitation and use of soap. More information is provided in the SOP.

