## Compensation/Reimbursement

Participation in the study is free of charge and caregivers do not receive any payments for participation in the study. Caregivers will be reimbursed for their transportation costs which will include a small amount to cover the costs of food purchase during the day of the clinic visit. A maximum of 20,000UGX will be given per return trip. Caregivers who do not receive LNS-LQ supplementation for their child during the study will still receive the same opportunities for medical review. In addition, a small token of appreciation, worth not more than 10,000 UGX will be provided to families of unsupplemented children.

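### The token given only to reference families may be soap, which could blur the secondary supplemented v reference comparison on diarrhoea and gut markers

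*Protocol*

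**What the plan says.** Three sections of the protocol describe the token, and all three confine it to the unsupplemented group.

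- Section 10, Random allocation: "Those not allocated to supplementation are given a token of appreciation (given at each follow-up clinic visit"; its worth is given as "valued at around 5000 UGX but not more than 10 000UGX, for example clothes soap".
- Section 16, Strategies to improve and monitor adherence, under incentives: "Any caregivers attending with unsupplemented children will also receive a small token which can be appreciated by the whole family, for example clothes soap".
- Section 28, Compensation/Reimbursement: "a small token of appreciation, worth not more than 10,000 UGX will be provided to families of unsupplemented children". No item is named here.

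No section gives soap or an equivalent item to the four supplemented arms. Section 13, which describes the reference condition, mentions family diet, counselling and follow-up but not the token.

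Elsewhere the protocol treats hygiene as relevant to the gut. The Background places environmental enteric dysfunction among children in settings "where they are frequently exposed to conditions of inadequate sanitation and hygiene" and regards it as a contributor to stunting. The WASH assessment at the first home visit records "water source, basic sanitation and use of soap". Section 17 lists diarrhoea episodes, stool myeloperoxidase, neopterin and alpha-1-antitrypsin, and blood citrulline as tertiary outcomes. The comparison that uses the reference arm is in section 18: "In secondary analysis, we will compare the 600 supplemented children with 150 unsupplemented".

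**The concern.** A randomised comparison isolates supplementation only if nothing else that could affect the outcome is handed out by arm. Here a household item goes to one arm repeatedly, and its only named example is a cleaning product. On the protocol's own reasoning, hygiene bears on gut inflammation, and gut inflammation bears on stunting.

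If the token is soap and soap does some good, the reference arm improves for a reason unrelated to diet. The supplemented v reference difference then shrinks, or reverses where the supplements do nothing. Diarrhoea and the gut markers are closest to the mechanism. Growth lies further along the chain, so an effect there over 12 weeks is less plausible.

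Randomisation does not protect against a difference introduced after allocation. The protocol names no measure of soap use after the first home visit, so such a difference would also go unseen.

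**Working it through.** **1. The plan's own figure for the affected comparison.** Section 18 states a detectable difference of 0.27 SD (4.9 mm of knee-heel length) for 600 v 150, with 5% significance, taken here as two-sided, and 80% power.

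- Formula: detectable difference = (1.960 + 0.842) × √(1/n₁ + 1/n₂).
- With 10% loss, n₁ = 540 and n₂ = 135. The root is 0.0962, and the result is 0.270 SD.
- 0.27 × 18.1 mm = 4.9 mm. The stated figure reproduces.

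**2. How many tokens can act.** Section 10 sets follow-up visits for all arms at weeks 2, 4, 8 and 12. Reading the token as given at follow-up visits only, there are four. The fourth is handed over at the visit where the final outcomes are collected, so three precede them.

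- Expected value: 3 × 5,000 = 15,000 UGX.
- Maximum: 3 × 10,000 = 30,000 UGX.

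**3. Which contrasts are touched.** The primary objective, the effects of milk protein isolate and whey permeate, is tested within arms A to D. No family in those arms gets the token, so it cancels. Only contrasts involving arm E are exposed.

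**4. What a bias would do if it existed.** The protocol gives no effect of soap, no effect of the supplements on diarrhoea and no diarrhoea rate. The soap effects below are assumptions and include zero.

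*Diarrhoea, supplements truly without effect.* Apparent risk ratio = 1 / (1 − soap reduction).

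| Assumed soap reduction in reference arm | Apparent ratio, supplemented v reference |
|---|---|
| 0% | 1.00 |
| 5% | 1 / 0.95 = 1.05 |
| 10% | 1 / 0.90 = 1.11 |
| 20% | 1 / 0.80 = 1.25 |

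If the supplements truly cut diarrhoea by 20% and soap by 10%, the ratio would read 0.80 / 0.90 = 0.89 instead of 0.80.

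*A continuous outcome, 540 v 135.* Power = Φ[(0.27 − b)/0.0962 − 1.960], where b is the assumed gain in the reference arm in SD. The last column is the two-sided rejection rate when the supplements have no effect. Where b is above zero, the excess over 5% points to harm.

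| b (SD) | Power for a true 0.27 SD benefit | Rejection rate with no supplement effect |
|---|---|---|
| 0 | 80% | 5.0% |
| 0.02 | 74% | 5.5% |
| 0.05 | 63% | 8.1% |
| 0.10 | 42% | 18.0% |

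These tables show how sensitive the comparison is. They do not estimate the bias.

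**The case against.** Five arguments can be made against the point.

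- **Soap is not fixed.** It is an example in two sections and absent from the third, and section 10 refers to a standard operating procedure for details. This stands. A reader might infer that the reference arm receives a regular soap supply and that the comparison is biased. The text supports only that it may. Still, a sole example given twice is what site staff are likely to follow, and nothing rules it out.
- **The mechanism is thin.** The item is laundry soap of small value. The Background speaks of sanitation and hygiene in general, and no section says households lack soap or would use more of it. This stands, and it is why zero belongs in the range.
- **Other asymmetries already exist.** Supplemented families make extra visits at weeks 6 and 10, and may receive extra sachets for other young children. Reference families know they have no supplement. The token is meant to support attendance. All true, but those differences follow from the design, whereas the choice of item is free.
- **Measuring soap use later would not repair it.** A reader might infer that the baseline-only WASH assessment is the defect. Soap use caused by the token is a consequence of allocation, and adjusting for it would not give a clean estimate. The argument stands: a later measure would describe the difference but not remove it.
- **Any valuable token can free money for soap or food.** True, so a neutral item reduces the problem but cannot guarantee its absence.

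A further tempting reading is that the main result is compromised. The documents do not support it, because the factorial contrasts do not involve the reference arm.

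**Conclusion.** The point holds as a minor, avoidable weakness. The protocol allows an item related to hygiene to be given repeatedly to one arm, in a trial that measures diarrhoea and gut inflammation. The exposure is limited to comparisons with the reference arm, chiefly on tertiary outcomes.

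The direction is conditional: if soap helps, the error runs against the supplements, so it would not produce a false claim of benefit. The size is unknown and may be nil. The conclusion assumes that soap, or something like it, is actually chosen and that it changes household hygiene enough to matter. The protocol establishes neither.

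**What to change.** In section 10 (Random allocation) and section 16, replace the soap example with an item of the same value that has no hygiene, food or health content. State that soap and food are not to be used as the token. Carry the same wording into the standard operating procedure. This keeps the token's purpose and its 5,000 to 10,000 UGX value, and costs only a change of item and of text.

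Alternatively, give the same item to all five arms. That removes the imbalance whatever the item is, at the small extra cost of supplying 600 more families.

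The change is optional and of low severity.
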